## Abstract

**Background:**

Inorganic nitrate has been shown to acutely improve working memory in adults, potentially by altering cerebral and peripheral vasculature. However, this remains unknown in adolescents. Furthermore, breakfast is important for overall health and psychological well-being. Therefore, this study will investigate the acute effects of nitrate and breakfast on working memory performance, task-related cerebral blood flow (CBF), arterial stiffness, and psychological outcomes in Swedish adolescents.

**Methods:**

This randomised crossover trial will recruit at least 43 adolescents (13–15 years old). There will be three experimental breakfast conditions: (1) none, (2) low-nitrate (normal breakfast), and (3) high-nitrate (concentrated beetroot juice with normal breakfast). Working memory (n-back tests), CBF (task-related changes in oxygenated and deoxygenated haemoglobin in the prefrontal cortex), and arterial stiffness (pulse wave velocity and augmentation index) will be measured twice, immediately after breakfast and 130 min later. Measures of psychological factors and salivary nitrate/nitrite will be assessed once before the conditions and at two-time points after the conditions.

**Discussion:**

This study will provide insight into the acute effects of nitrate and breakfast on working memory in adolescents and to what extent any such effects can be explained by changes in CBF. This study will also shed light upon whether oral intake of nitrate may acutely improve arterial stiffness and psychological well-being, in adolescents. Consequently, results will indicate if nitrate intake from beetroot juice or if breakfast itself could acutely improve cognitive, vascular, and psychological health in adolescents, which can affect academic performance and have implications for policies regarding school meals.

**Trial registration:**

The trial has been prospectively registered on 21/02/2022 at https://doi.org/10.1186/ISRCTN16596056. Trial number: ISRCTN16596056.

## Introduction

Inorganic nitrate can be obtained from diet, through sources such as rocket (rucola), spinach, lettuce, and beetroot [1], with green leafy vegetables contributing to the majority of nitrate consumption [2]. Dietary nitrate is converted into nitrite in the oral cavity, with some of the consumed nitrite being reduced in the stomach to nitric oxide (NO) [3]. However, nitrite is also absorbed into the bloodstream and distributed across the tissues in the body. There, nitrite can be reduced to bioactive NO by several different processes [4]. NO is an important molecule involved in many systemic and cerebral physiological processes. Previous studies have demonstrated its beneficial effects on blood pressure [5–9], endothelial function [8, 9], arterial stiffness [3, 7, 10], and mitochondrial respiratory efficiency in human skeletal muscle [11], whereas inadequate NO has been associated with greater risk for cognitive decline [12, 13]. Despite this knowledge, randomised controlled trials (RCTs) examining the effects of dietary nitrate on cognitive function have been few, with small sample sizes, and only in adult populations, resulting in mixed results [14]. Therefore, more studies of higher quality and in other populations that could benefit from the effects of nitrate, such as adolescents, are needed.

NO regulates many neurobiological processes in the brain and vascular system, such as the regulation of synaptic plasticity, immune response, vascular tone, and neurotransmission, thus promoting cerebral blood flow [15]. A diet rich in nitrate can promote this cascade from nitrite to NO, leading to physiologic effects that may improve prefrontal-dominate cognitive tasks, such as tasks of executive function that are necessary for everyday performance [16]. Executive functions are mental processes that require concentration and attention, with working memory being a core executive function. Working memory involves retaining and manipulating limited information temporarily to be used immediately, such as in problem solving and decision making [17]. A previous meta-analysis of RCTs including adult populations found mixed results on the effect of nitrate on cognitive performance, partly due to the large heterogeneity in types of cognitive tests used and small sample sizes [14]. However, two previous RCTs showed beneficial effects of nitrate on executive function, one including a working memory test [16, 18]. In children and adolescents working memory has been shown to be the strongest contributing component in the association between executive functions and academic performance compared with other executive function components [19]. Thus, working memory is an important function for performing well academically, and a nitrate-rich diet may enhance this, as seen in older adults [20].

Dietary nitrate and NO have been suggested to enhance neurovascular coupling during cognitive tasks [21]. Neurovascular coupling involves an enhancement in regional cerebral oxygen metabolism coupled to a cognitive task, in order to meet the metabolic demands of neural tissues [22, 23]. As a result, there is an excess of cerebral blood flow (CBF; measured as an increase in oxygenated haemoglobin [oxy-Hb] and a decrease in deoxygenated haemoglobin [deoxy-Hb] concentrations) [24] to the activated regions [22, 23]. Increases in CBF to relevant cerebral regions have been observed during increased cognitive workload [25], where a more pronounced response can occur for more difficult tasks [26]. One study found in older adults that a high intake of nitrate-rich foods increased regional cerebral perfusion in the prefrontal cortex (the part of the brain associated with executive functions and working memory), but not globally [20]. Another intervention study of young healthy adults (mean age 21.3 years), demonstrated that ingestion of dietary nitrate from beetroot juice improved working memory on a revised serial subtraction task compared with the placebo condition [16]. The same intervention study measured changes in CBF (indicated by changes in total haemoglobin) through functional near-infrared spectroscopy (fNIRS) and found nitrate to modulate CBF during the serial subtraction task [16]. However, more studies are needed to disentangle these effects as conflicting results have also been demonstrated on the effects of nitrate on cognitive function and CBF [14]. Thus, a better understanding is needed into NO’s potential mechanistic effects on working memory performance and CBF changes particularly in adolescents.

Reduced availability and functionality of NO in the body has been associated with endothelial dysfunction and cardiovascular disease (CVD) [27–29]. Arterial stiffness is an independent predictor of cardiovascular risk [30] and is measured via pulse wave velocity (PWV) and augmentation index (AIx). Two meta-analyses of RCTs, of adults, have reported that intake of inorganic nitrate reduced PWV and AIx [3, 31]. This reduction was observed in one of the meta-analyses specifically from inorganic nitrate from beetroot, suggesting that this dietary source may well have a beneficial effect on certain cardiovascular risk factors [31]. Despite this, all of these studies have been in young and older adults and in mixed health populations. To our knowledge, no studies have investigated the effects of nitrate on vascular health in adolescents, thus the effects of nitrate consumption on arterial stiffness remains to be explored in this population.

More widely studied topics in adolescents are the effects of breakfast consumption on cognitive function, cardiovascular health, and psychological factors. There are no specific dietary recommendations for breakfast composition in Sweden. Still, Swedish dietary guidelines can be applied to breakfast, such as: increasing fruit, vegetable, nut, and seed intakes and opting for wholegrain cereals as well as low-fat dairy options [32]. Breakfast consumption has been suggested to be linked with numerous health benefits in adolescents including cognitive performance and cardiovascular health [33]. Adolphus et al. [33] found that consuming breakfast compared to fasting to have positive and same morning effects on cognitive performance. Cognitive tasks requiring attention, executive functioning, and memory were completed more reliably in those consuming breakfast compared to those omitting breakfast among adolescents [33]. In contrast, irregular breakfast habits have been associated with lower academic success [34]. In regards to cardiovascular health, results from the Healthy Lifestyle in Europe by Nutrition in Adolescence study [35] showed that consuming breakfast regularly was associated with a healthier cardiovascular profile (e.g. lower waist circumference, blood pressure, and total content of high-density lipoproteins). Furthermore, in a sample of 795 adolescents, eating breakfast regularly was found to be inversely associated with multiple CVD risk factors [36]. Adolescents that habitually consume breakfast are more likely to have a higher diet quality [37], eat more fruits and vegetables [38], and have a decreased risk of being overweight and obese [39]. Despite this, the prevalence of breakfast skipping in a sample of 2929 adolescents across nine European countries was found to be 29% [35]. The same study found that females were more likely to be breakfast skippers than males [35]. Moreover, in a recent cross-sectional study with a sample size of 1139, around 40% of Swedish adolescents skipped breakfast at least one time per week [38]. Therefore, still to this day, this important meal is being skipped by many adolescents. In addition, very few studies have been performed looking at breakfast compositional differences than comparing breakfast to breakfast omission [33]. Therefore, the combination of nitrate-rich foods and breakfast on cognitive performance has not been previously examined. Furthermore, whether the effect of breakfast on cognitive performance is explained by CBF changes is unknown. One study of female university students found that skipping breakfast can have negative physiological effects on CBF [40]. Further study is needed to test whether the same results occur in adolescents and on a working memory-related CBF. This study will be the first to investigate various breakfast compositions on cognitive function, and in relation to cerebral physiological effects.

Breakfast consumption compared to breakfast omission has also been found to have positive effects on mood and psychological factors in adolescents [41, 42]. Cooper et al. found that breakfast consumption led to higher self-reports of energy and satiety as well as lower self-reports on tiredness in adolescents [41]. Additionally, higher self-reports of alertness and contentment have been described in those that consumed breakfast compared with those who skipped breakfast [42]. Changes in one’s state of psychological well-being and how one is feeling after breakfast consumption may facilitate attention and motivation in adolescents when performing cognitive tasks, thus influencing cognitive function [33]. Therefore, it is useful to measure mood and other psychological factors when assessing cognitive function.

The acute effects of nitrate on cognitive function, cognitive task-related CBF, vascular health, and psychological factors are believed to not have been studied before in adolescents nor has the acute effects of breakfast on these aforementioned outcomes. Thus, there is a large lack of knowledge and a need to investigate the effects of nitrate and breakfast on these important health outcomes. Consuming nitrate-rich beetroot juice with breakfast is considered to be an achievable, ecologically valid, and relatively low-cost method to increase consumption of dietary nitrate. Therefore, the results from this intervention could help to promote consuming nitrate-rich beetroot juice or other nitrate-rich vegetables and could lead to an increase in overall nitrate-rich vegetable consumption, in this population. Nevertheless, adherence to nitrate-rich beetroot juice or vegetables could be a challenge in the adolescent population. Previous research has found the consumption of fruit and vegetables amongst Swedish adolescents to be below 50% of the recommended intake [43]. This study will indirectly explore and provide insight into the adherence and acceptance of consuming nitrate-rich beetroot juice with breakfast in adolescents.

### Aims and research questions

The primary aim of this study will be to assess the effects of having a high-nitrate breakfast on working memory in 13- to 15-year-old adolescents compared with a regular breakfast (referred to as low-nitrate breakfast) or no breakfast. Secondly, we aim to test the effect of having a high-nitrate breakfast compared with a low-nitrate breakfast or no breakfast on cognitive task-related CBF, arterial stiffness, and psychological factors. Thirdly, we aim to examine the effects of having a regular breakfast (defined as low nitrate breakfast) compared with no breakfast on working memory, task-related CBF, arterial stiffness, and psychological factors. Finally, we want to test whether salivary nitrate/nitrite levels will differ across breakfast conditions. The research questions are divided into two parts.

#### Part I–Primary research question

Does having a high-nitrate breakfast significantly improve performance on working memory tests compared with having a low-nitrate breakfast or having no breakfast in 13- to 15-year-old adolescents?

#### Part II–Secondary research questions

Is there a statistically significant difference in cognitive task-related CBF (oxy-Hb and deoxy-Hb), arterial stiffness, and psychological measures 130 min after a high-nitrate breakfast compared with a low-nitrate or no breakfast?Is there a statistically significant difference in working memory, cognitive task-related CBF, arterial stiffness, and psychological factors 130 min after having low-nitrate breakfast compared with no breakfast?Will salivary nitrate/nitrite levels differ across breakfast conditions?

### Hypotheses

#### Part I

Working memory performance will significantly improve from immediately after the breakfast (time point 1) to 130 min after the breakfast (time point 2) in the high-nitrate breakfast condition.
This improvement will significantly differ from the low-nitrate or the no breakfast conditions, where there will be no change or a reduction in working memory performance.

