#### Part II

2. The CBF parameter of oxy-Hb will significantly increase from time point 1 to time point 2 for all breakfast conditions.
This change will be significantly greater for the high-nitrate breakfast condition compared with the low-nitrate and no breakfast conditions.3. Deoxy-Hb will decrease for all conditions from time point 1 to time point 2.
The decrease will be significantly greater for the high-nitrate breakfast compared with the low-nitrate and the no breakfast conditions.4. Arterial stiffness will significantly decrease after the high-nitrate breakfast condition.
The decrease will be significantly greater in the high-nitrate breakfast compared with the low-nitrate and no breakfast conditions.5. Psychological factors (i.e. mood, alertness, and less sleepiness) will improve from time point 1 to time point 2 for the high-nitrate condition
The improvement in psychological factors will be significantly greater for the high-nitrate breakfast compared with the low-nitrate and no breakfast conditions.6. Working memory performance will significantly improve in the low-nitrate breakfast condition from time point 1 to time point 2.
This improvement will be significantly different from the no breakfast condition.7. Oxy-Hb will increase from time point 1 to time point 2 for the low-nitrate breakfast condition.
This increase will be significantly greater for the low-nitrate breakfast compared with the no breakfast condition.8. Deoxy-Hb will significantly decrease for the low-nitrate breakfast condition.
This decrease will be significantly different from the no breakfast condition.9. Arterial stiffness will significantly decrease in the low-nitrate breakfast condition.
This decrease will be significantly different from the no breakfast condition.10. Psychological factors (i.e. mood, alertness, and less sleepiness) will improve from time point 1 to time point 2 for the low-nitrate breakfast condition
This difference will be significantly greater for the low-nitrate breakfast condition compared with the no breakfast condition.11. Salivary nitrate/nitrite levels will be significantly higher after the high-nitrate breakfast at time point 1 and time point 2 compared to the low-nitrate and no breakfast conditions, and higher for low-nitrate vs. no breakfast.

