### Statistical methods

#### Working memory, psychological factors, arterial stiffness, and nitrate/nitrite analysis

Linear mixed effect models, with an unstructured covariance structure, will be used to estimate within condition changes in working memory reaction time and accuracy, psychological factors, arterial stiffness, and nitrate/nitrite concentrations from time point 1 to time point 2 using Stata/SE 17.0 (StataCorp, LLC, Texas, USA). Additional models will be performed with condition and time interactions to assess between condition changes in mean differences in these outcomes.

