#### Cerebral blood flow analysis

The task-related relative changes (Δμmol) in oxy-Hb and deoxy-Hb will be estimated using MATLAB-based software NIRS Brain AnalyzIR Toolbox (https://github.com/huppertt/nirs-toolbox [67]). Oxy-Hb will be the predominant cerebral blood flow outcome as it has previously been reported to be the most sensitive indicator of neural activation [68]. FNIRS probe registration will be individualised to account for anatomical differences and probe placement, by using head circumference, nasion-inion, and pre-auricular distances from each participant. Quality check of each signal will be initially performed, including checking the relative coefficient of variation (CV%) for each channel. A CV% less than 15% will indicate good signal quality. Poor signal quality will be dealt with in the statistical analysis. Raw voltage will then be converted to optical density and subsequently to haemoglobin concentrations based on the modified Beer-Lambert law [52]. Data will be processed and analysed in a similar manner outlined in Heiland et al. [52]. Minimal manipulation will be performed on the signals as suggested by Santosa et al. [67]. First level statistics will involve estimating the fNIRS parameters during the 1-, 2-, and 3-back tasks (each 35 sec duration) relative to the baseline (20 sec rest). Brain activation will be predicted using a general linear model (GLM) with a canonical design matrix and an autoregressive pre-whitening approach with iteratively reweighted least squares (AR-IRLS) for each source-detector pair. The AR-IRLS approach will be used because it reduces the false-discovery rate [69]. Short-separation regressors will be used to control for type I errors caused by systemic physiology and motion artefacts. The GLM will yield regression coefficients (betas) for each channel in each n-back task and condition that will be used in the second-level analyses (group-level analysis). This will entail the coefficients of Δoxy- and Δdeoxy-Hb each being averaged across the prefrontal region, and separately by left and right prefrontal hemispheres for each n-back task and condition. A False Discovery Rate (FDR) correction using a Benjamini-Hochberg procedure will be used to correct for multiple comparisons (*q-value* = FDR-adjusted *p ≤ 0*.*05*). Linear mixed effect models will be employed with Δoxy- and Δdeoxy-Hb as dependent variables, with condition and time as fixed effects and subject as a random effect to assess within and between condition differences in CBF parameters comparing the n-back tasks. Linear mixed effects models with maximum likelihood estimation will help to deal with potential missing data. Number of missing data will also be reported and checked for missing data mechanisms. Additional, linear mixed models will be performed to assess intervention effects including time and condition as interaction terms.

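### The analysis text puts within-condition change first and calls the randomised condition-by-time comparison additional, although the primary question is between conditions

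*Protocol article*

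**What the plan says.** Under Statistical methods, the first subsection covers working memory (the primary outcome), psychological factors, arterial stiffness and nitrate/nitrite. It says that the linear mixed models "will be used to estimate within condition changes in working memory reaction time and accuracy" and in the other outcomes listed there, from time point 1 to time point 2. The comparison between conditions follows: "Additional models will be performed with condition and time interactions to assess between condition changes in mean differences in these outcomes".

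The Cerebral blood flow analysis subsection differs somewhat. Its first mixed model has condition and time as fixed effects and is meant to cover differences both within and between conditions. The interaction models are again called additional, although they carry the intervention question: "linear mixed models will be performed to assess intervention effects including time and condition as interaction terms".

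Hypotheses 1 to 10 have two parts. The first is a change within a condition, and six of them (1, 2, 4, 6, 8 and 9) state that change as significant; hypothesis 1 begins "Working memory performance will significantly improve". The second is a difference between conditions; for hypothesis 1 it reads "This improvement will significantly differ from the low-nitrate or the no breakfast conditions". Hypothesis 11, on salivary nitrate/nitrite, is purely between-condition. The primary research question asks only how the high-nitrate breakfast compares with the other two conditions.

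**The concern.** Randomising the order of conditions protects one thing: the comparison of conditions. Within any single condition, time and treatment move together. Practice on the n-back tasks, fatigue, longer fasting and the 80-minute sitting period can all shift scores between the two time points whatever was eaten, and a within-condition p-value cannot tell these from a nitrate or breakfast effect.

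The protocol expects such movement for two outcomes. Hypothesis 2 says "The CBF parameter of oxy-Hb will significantly increase from time point 1 to time point 2 for all breakfast conditions", which includes no breakfast, and hypothesis 3 predicts a fall in deoxy-Hb in every condition.

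Two opposite errors are possible, depending on how the two-part hypotheses are read. If the first clause is reported as a finding in its own right, a shared trend can support it with no effect of the intervention. If both clauses are required, a real benefit can be lost because a general decline over the morning cancels it within the condition. The protocol does not say which reading applies.

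**Working it through.** **Inputs.** From Sample size: two-sided α = 0.05, power 0.80, a comparison of two dependent means, effect sizes 0.63 (nitrate on working memory) and 0.67 to 0.48 (breakfast on psychological factors), n = 36 before dropout and 43 in total. Assumed, because the protocol gives no figure: the size of any shared time trend, in SD of the time point 1 to 2 change score; and the correlation ρ of change scores across conditions, taken as 0 or 0.5. A paired t test on change scores stands in for the mixed model with complete data.

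**Reproducing the plan's figures.** Exact power comes from the noncentral t distribution with n − 1 degrees of freedom and noncentrality d√n. For 80% power, d = 0.63 needs 22, d = 0.67 needs 20 and d = 0.48 needs 37. The stated 36 has power 0.800 after rounding, so the difference is trivial. The total is 36 + 7 = 43. The same formula is used below.

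**Shared trend, no condition effect.** The chance that the test within one condition is significant at n = 36 (critical t = 2.03):

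| Assumed drift (SD of change) | d√36 | Within-condition test significant |
|---|---|---|
| 0.20 | 1.20 | 21% |
| 0.33 | 1.98 | 49% |
| 0.48 | 2.88 | 80% |

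At n = 43 the same drifts give 25%, 56% and 87%.

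**The between-condition contrast under the same drift.** If every condition drifts by δ, the contrast of changes is (δ + effect) − δ = effect, so the drift cancels. A simulation of three conditions with no condition effect (40,000 runs; drifts from 0 to 0.63 SD; n = 36 and 43; ρ = 0 and 0.5) gave a two-sided rejection rate of 4.8% to 5.4% for high-nitrate against no breakfast, at every drift.

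**Both clauses required, no condition effect.** In the same simulation, a significant high-nitrate improvement together with superiority over both comparators occurred in about 0.2% to 0.5% of trials. Together with superiority over at least one comparator, it occurred in at most about 4.6%.

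**Shared decline with a real benefit.** Take a decline of 0.30 SD in every condition and a true nitrate benefit of 0.48 SD. The net change within the high-nitrate condition is 0.48 − 0.30 = 0.18 SD; d√36 = 1.08, and the within-condition test is significant in about 18% of trials. For the contrast, the SD of the difference between two change scores is √(2(1 − ρ)). At ρ = 0.5 this is 1, the standardised effect is 0.48 and power is 80%. At ρ = 0 it is √2, the effect is 0.48/√2 = 0.34 and power is about 51%. In both cases the contrast is far more likely than the within-condition test to find the benefit.

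**The case against.** The best defence is that the randomised comparison is planned. The primary aim and research questions are comparative, each of hypotheses 1 to 10 has a between-condition clause, and interaction models are named for all these outcomes. Additional may mean no more than a further model, and order of mention is not a declared hierarchy. For cerebral blood flow, the first model already covers both kinds of difference. The protocol also acts against practice effects, with practice at familiarisation and again on each test day. Ranking analyses as confirmatory or descriptive is often left to a fuller document.

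Much of this stands, and it rules out three stronger readings that a reader might infer.

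- That a shared trend would confirm the hypotheses as a whole. It would not: it can meet only the first clause, and the second needs a difference between conditions.
- That the protocol expects a trend for every outcome. It predicts change in all conditions only for oxy-Hb and deoxy-Hb. For working memory, hypothesis 1 expects the two comparator conditions to stay level or decline, so a shared improvement would contradict it.
- That the protocol sets within-condition significance as a formal success rule, or would infer a difference from significance in one condition and its absence in another. It states neither rule.

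The defence does not remove the ordering. The article names within-condition change as what the models for the primary outcome estimate, writes significance into six within-condition clauses, and leaves open how the two clauses combine. That is text the article contains, not detail it omits.

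**Conclusion.** The point holds in a limited form. For the primary outcome, the analysis listed first does not answer the primary research question, and the one that does is labelled additional. As written, the plan allows within-condition significance to be reported as support for part of the primary hypothesis, or to block a real benefit if both clauses are required.

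The percentages illustrate the mechanism under assumed drifts; they do not predict this trial's error rate. The claim of a difference between conditions is not inflated: the planned contrast stays near 5% whatever the drift, and requiring both clauses does not raise the false-positive rate. The 80% contrast power in the decline example rests on an assumed correlation of 0.5 between change scores. The sample size is not affected.

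**What to change.** In both Statistical methods subsections, name the condition-by-time contrasts as the confirmatory analysis for hypotheses 1 to 10: high minus low, high minus none, and low minus none in the time point 1 to 2 change. Report within-condition changes as descriptive estimates with confidence intervals, and remove within-condition significance from those hypotheses.

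In the same edit, reconcile two statements about working memory after the low-nitrate breakfast: hypothesis 6 predicts a significant improvement, while hypothesis 1 expects that condition to stay level or decline.

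This is a free improvement. The interaction models are already planned, so only wording changes; no new data, participants or models are needed.

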### Outcome measures

**Primary outcome:** Working memory.

**Secondary outcomes:** Cognitive task-related CBF, arterial stiffness, psychological factors (mood, alertness, and sleepiness), and salivary nitrate/nitrite concentrations.

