#### Working memory

N-back paradigms will be used to assess working memory performance, consisting of the 1-, 2-, and 3-back tests [51] at two time points (time points 1 and 2) after the breakfast experimental conditions (**Fig 2**). The n-back paradigms are computerised numerical versions where the participants will indicate if the digit presented on the screen is the same digit that was presented 1 digit earlier (1-back), 2 digits earlier (2-back), or 3 digits earlier (3-back) (**Fig 3**). Participants will indicate this via a key press within a 2000 ms period from the onset of the digit, whereby each digit is presented for 1500 ms with an inter-stimuli interval of 500 ms. E-Prime 2.0 (Psychology Software Tools) was used to create the n-back tests and for capturing the data. Before each n-back test, participants will be required to stare at a white dot on a black screen and count from zero to reduce mind-wandering for 20 secs, which will be used as the baseline. Average reaction time (m/s) of correct responses and accuracy (number of correct responses) will be measured for each n-back test across the 3 blocks of 20-digit sequences each, with each n-back test lasting 35 secs.

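### The primary hypothesis fixes neither one working memory measure nor one comparator, and it contradicts a secondary hypothesis about the low-nitrate breakfast

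*Protocol article*

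**What the plan says.** All references are to the protocol article.

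- **Outcome measures** gives "Primary outcome: Working memory" and names no variable, load or summary score.
- **Working memory** describes a task "consisting of the 1-, 2-, and 3-back tests" and adds: "Average reaction time (m/s) of correct responses and accuracy (number of correct responses) will be measured for each n-back test".
- **Part I, primary research question** asks about high-nitrate "compared with having a low-nitrate breakfast or having no breakfast in 13- to 15-year-old adolescents".
- **Hypotheses, Part I** has two limbs. Working memory must improve significantly between the two time points under high nitrate, and "This improvement will significantly differ from the low-nitrate or the no breakfast conditions". The same sentence predicts that the comparators will stay flat or get worse.
- **Hypotheses, Part II**, Hypothesis 6: "Working memory performance will significantly improve in the low-nitrate breakfast condition from time point 1 to time point 2".
- **Statistical methods** lists reaction time and accuracy among the outcomes for mixed models, with condition-by-time interactions for the between-condition comparisons. It gives no lead variable, success rule or adjustment for working memory.
- **Cerebral blood flow analysis** contains the only correction stated: "A False Discovery Rate (FDR) correction using a Benjamini-Hochberg procedure will be used to correct for multiple comparisons".
- **Experimental conditions** defines high-nitrate as the regular breakfast plus concentrated beetroot juice.

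**The concern.** A primary hypothesis should tell the reader in advance which result would confirm it. Here two choices are open: which of six measures counts, and whether high-nitrate must beat one comparator or both. If these are settled after the results are known, the nominal 5% level no longer describes the risk of a false primary claim.

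The comparators also answer different questions. Against the low-nitrate breakfast, the food is held constant and only the juice is added. Against no breakfast, food and nitrate change together, so a difference there does not show that nitrate did anything. If the *or* is taken literally, that second contrast alone could meet the between-condition limb.

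Finally, the plan makes two opposed predictions for the low-nitrate condition on the primary outcome, so it is unclear what pattern the investigators regard as support.

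**Working it through.** **1. The plan's own figure.** Sample size uses a two-sided paired comparison at α = 0.05 and 80% power. With the noncentral t distribution, the stated effect of 0.63 for nitrate on working memory gives n = 22 (power 0.804), as printed. The calculation is for a single test, with no allowance for several primary contrasts. The article states no familywise error rate.

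**2. Count of contrasts.** 3 loads × 2 variables = 6 measures. 6 measures × 2 comparators = 12 between-condition contrasts.

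**3. Ceiling under independence.** Chance of at least one false positive = 1 − 0.95^k.
- k = 2: 9.75%
- k = 6: 26.5%
- k = 12: 46.0%

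**4. Allowing for correlation.** The article gives no correlations between measures, so they are assumed. The simulation used n = 36, no condition effect and 10,000 runs per cell. Change scores were independent between conditions, so the two contrasts share the high-nitrate arm and correlate 0.5. Each test is at two-sided 5%.

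| Correlation between measures | Any of 12, two-sided | Any of 12, favouring high nitrate | Favourable, plus within-condition improvement on the same measure, no time trend | As previous column, common improvement of 0.3-0.5 SD | Six measures vs low-nitrate only, two-sided |
|---|---|---|---|---|---|
| 0 | 43% | 25% | 8% | 23-24% | 27% |
| 0.3 | 41% | 22% | 7% | 21% | 24% |
| 0.5 | 36% | 18% | 6% | 18% | 21% |
| 0.7 | 29% | 14% | 5% | 14% | 17% |
| 0.9 | 20% | 10% | 3% | 9-10% | 11% |

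**5. If both comparators must be beaten on the same measure.** A separate simulation (200,000 draws, contrasts correlated 0.5, measure correlation 0 to 0.9, any of the six measures sufficing) gives about 2.5-5% two-sided and 1.2-2.7% favouring high nitrate when no condition has any effect. If breakfast has a strong real effect and nitrate none, the no-breakfast contrast stops protecting. The six low-nitrate contrasts then set the error: up to 26.5% two-sided, or 1 − 0.975^6 = 14.1% in the favourable direction, if independent.

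**6. Hypothesis 1 beside Hypothesis 6.** Same outcome, same condition, same interval. Hypothesis 1 has the low-nitrate condition unchanged or worse; Hypothesis 6 has it significantly better. Both cannot be true.

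**7. Cost in power at an effect of 0.63.**
- One measure, high- versus low-nitrate only, at 5%: 96% power at n = 36.
- Six measures against low-nitrate, Bonferroni (0.05/6 = 0.0083): n = 35 for 80% power; 83% at n = 36.
- All 12, Bonferroni (0.05/12 = 0.0042): n = 39 for 80% power; 76% at n = 36 and 86% at n = 43.

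**The case against.** The strongest reply is that the article sets no rule under which any one of 12 results suffices.

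- **The word *or* is ambiguous.** The secondary research question also joins the comparators with *or*, yet the matching Hypotheses 2-5 join them with *and*. The Part I sentence continues in the plural. Reading it as both comparators is natural, and under a complete null that reading keeps the error near or below 5%. This stands, but it shows that the rule needs stating.
- **No passage says one measure is enough.** A single model across loads is not excluded. This stands too: the 12-contrast figure is conditional on how the gap is filled.
- **The within-condition limb restrains the error.** It does when there is no time trend (3-8%). It is not dependable control, because a shared improvement satisfies it in every condition. The article itself schedules practice at familiarisation to reduce practice effects.
- **An analysis plan not shown may add an adjustment.** That is possible, so nothing here says the trial has no error control. The point concerns what the article states: an open primary outcome, an unclear comparator rule, correction placed only with a secondary outcome, and two opposed predictions.
- **A pure breakfast effect would be visible.** Low-nitrate versus no breakfast is prespecified for working memory, and high- versus low-nitrate is part of the primary comparison. A reader might infer that such an effect would pass unnoticed as a nitrate success. The documents do not support that; they only leave open whether the no-breakfast contrast alone could count as primary success.
- **The conflict between Hypotheses 1 and 6 is not a loophole.** Each also requires a between-condition difference, so it is wrong to say that almost any low-nitrate result would confirm one of them. The contradiction itself remains.

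**Conclusion.** The point holds in a bounded form. The primary hypothesis names neither a single measure nor a clear comparator rule, and no correction is stated for working memory. The size depends on the reading:

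- any of 12 contrasts, unadjusted: about 20-46% two-sided, about 10-25% favouring high nitrate;
- a favourable contrast plus within-condition improvement on the same measure: about 3-8% with no time trend, about 9-24% with a common practice trend;
- both comparators beaten on the same measure: about 2.5-5% two-sided if no condition has any effect, rising if breakfast works and nitrate does not.

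These ranges rest on assumed correlations between measures (0 to 0.9; the 46% end assumes all 12 tests independent) and on an assumed time trend. The documents give neither.

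A reader might infer that a false-positive primary claim is likely. That is not supported: even the independence ceiling is below one half, and it counts results in which high nitrate is worse. Two conclusions need no calculation: only high- versus low-nitrate isolates nitrate, and Hypotheses 1 and 6 are incompatible as written.

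**What to change.** Before the outcome data are analysed, in a dated amendment or the analysis plan:

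1. Name one working memory score, for example reaction time of correct responses across the three loads, from one model with load as a factor. Another single score would serve if justified in advance.
2. Make the high- versus low-nitrate difference in change the primary test, two-sided 5%.
3. Test high-nitrate versus no breakfast next in fixed order, or replace *or* by an explicit rule saying whether one or both comparators must be beaten.
4. Treat the remaining measures and single-load results as secondary, with adjustment; the Benjamini-Hochberg procedure already planned for CBF would do.
5. Base the conclusion on between-condition contrasts, not on significance within a condition.
6. Reconcile Hypotheses 1 and 6, preferably as between-condition statements.

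The cost is wording. No participants are added: if the nominated score has the article's assumed effect of 0.63, the single test has 96% power at n = 36. The downside is that one measure must be nominated, and an effect confined to one load or to accuracy could then be claimed only as a secondary result.
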